## Abstract

**Background:**

Lung ultrasound (LUS) in combination with a biomarker has not yet been studied. We propose a clinical trial where the primary aims are: 1. To assess whether an algorithm with LUS and procalcitonin (PCT) may be useful for diagnosing bacterial pneumonia; 2. To analyse the sensitivity and specificity of LUS vs chest X-ray (CXR).

**Methods/design:**

A 3-year clinical trial. Inclusion criteria: children younger than 18 years old with suspected pneumonia in a Paediatric Intensive Care Unit. Patients will be randomised into two groups: Experimental Group: LUS will be performed as first lung image. Control Group: CXR will be performed as first pulmonary image. Patients will be classified according to the image and the PCT: a) PCT < 1 ng/mL and LUS/CXR are not suggestive of bacterial pneumonia (BN), no antibiotic will be prescribed; b) LUS/CXR are suggestive of BN, regardless of the PCT, antibiotic therapy is recommended; c) LUS/CXR is not suggestive of BN and PCT > 1 ng/mL, antibiotic therapy is recommended.

**Conclusion:**

This algorithm will help us to diagnose bacterial pneumonia and to prescribe the correct antibiotic treatment. A reduction of antibiotics per patient, of the treatment length, and of the exposure to ionizing radiation and in costs is expected.

**Trial registration:**

NCT04217980.

## Background

Pneumonia is responsible for more than 2 million child deaths around the world; it is the leading cause of childhood morbidity and mortality [1]. Moreover, severe lower respiratory infection is the most common cause of admission to paediatric intensive care units (PICUs) [2]. Around 60–70% of these have a viral etiology [3]. For physicians, it is important to differentiate between viral and bacterial infection because each entails a different therapeutic approach (whether antibiotics are indicated and the treatment duration), a different prognosis in the short and long term, and requires a different hospital isolation policy [4, 5]. It is challenging to rule whether a case of pneumonia is viral or bacterial in origin [6–8]. Clinical symptoms are similar and although conventional chest radiographs (CXR) have traditionally been considered the best diagnostic option [9], the specificity of CXR for determining bacterial etology remains low. Chest computed tomography may detect smaller pulmonary consolidations not visible via CXR, but it cannot be routinely performed on critically ill patients due to cost, exposure to radiation, and transportation risk [9]. Therefore, there is a need to have an examination tool that can be used at the patient’s bedside and which is easily reproducible to help detect lung consolidations. LUS has recently emerged as a radiation-free technique; it is non-invasive, with a high interobserver [10] agreement for lung pathologies such as consolidation [11], pleural effusion [12], interstitial syndrome [13], and pneumothorax [14]. To determine the etiology, conventional microbiology tests such as blood culture, pleural aspiration, and bronchoalveolar lavage are usual practices, but some of these are invasive, may not detect all etiologies [15], and the results may not be immediate.

Besides this, the use of biomarkers such as procalcitonin (PCT) has become more widespread during the past 10 years, helping clinicians diagnose bacterial etiology, especially in patients who have only had a fever for a few hours or those admitted to intensive care units [16–20]. The use of PCT has allowed for a decrease in antibiotic prescription [21, 22], even in nosocomial and community pneumonia [23, 24]. Despite its role in the diagnosis of pneumonia, PCT values without any other tests may not be a complete diagnostic biomarker for pneumonia.

Quality of care is defined by the World Health Organization as medical care in which the patient is diagnosed and treated correctly, according to current medical knowledge (scientific and technical quality), and to their biological factors (optimal state of health to attain), with a minimum cost (efficiency), minimum possible exposure to risk for more harm, and maximum patient satisfaction [25]. At the hospital level, a quality assurance plan should include different levels of action. The first step is level 1 of quality promotion, which requires institutional support and the availability of clinical and quality protocols. The second step is the research level: descriptive studies for detecting and quantifying a specific situation or health issue, and the use of databases or specific studies to evaluate health services, among others.

Therefore, we propose this clinical trial, based on combining LUS and PCT in an algorithm with the aim to improve quality of care in children with pneumonia in a PICU. We hypothesize that the diagnostic performance of LUS and PCT will be better than conventional CXR.

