### Study aim

Our primary goal is to improve the quality of care in children with suspected community or nosocomial pneumonia in a PICU.

The main objectives are:
To assess whether a diagnostic algorithm for pneumonia that combines LUS and PCT may be useful in indicating and determining the duration of antibiotic treatment.To analyse the sensitivity and specificity of LUS, compared to CXR, for severe community or nosocomial pneumonia.

The secondary aims are:
To quantify the irradiation dose avoided using LUS to replace CXR, and to determine if there is an associated decrease in costs.To analyse interobserver agreement in LUS

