### Methodology

The first thing to do will be to obtain consent from the parent(s) or legal guardian(s).

Patients who meet the inclusion criteria and sign the inform consent were randomly assigned to two groups using the “random” function in MS-Excel XP® program. A binary series of random numbers were generated according to the procedure described by Friedman. To procure a similar number of patients in both groups, the procedure created the sequence through a balanced block sampling. The series of numbers were held by the principal investigator and depending on the number of the patient tit was be assigned to on or another group. A total of 8 physicians enrolled participants, and the principal investigator assigned participants to interventions, depending on the randomized list. (Fig. 1)
Experimental Group 1: The paediatrician-researcher (PR) performs the LUS at admission/suspicion as the first lung image test. If the paediatrician assistant (PA) requires a CXR, it can be performed, but the PR will not see the CXR. Patients will be subdivided into 3 groups:
If PCT is < 1 ng/mL and LUS is not suggestive of bacterial pneumonia (normal or viral), the patient will not receive an antibiotic.If LUS is suggestive of bacterial pneumonia, regardless of PCT value, an antibiotic will be recommended.If LUS is not suggestive of bacterial pneumonia, but PCT values are > 1 ng/mL, an antibiotic will be recommended to cover other infectious etiologies.Control Group 2: CXR will be performed as a first lung image test. Criteria to start an antibiotic will depend on the current unit protocol.
If PCT is < 1 ng/mL and CXR is not suggestive of bacterial pneumonia (normal or viral), the patient will not receive an antibiotic.If CXR is suggestive of bacterial pneumonia, regardless of PCT value, an antibiotic will be recommended.If CXR is not suggestive of bacterial pneumonia, but PCT value is > 1 ng/mL, an antibiotic will be recommended to cover other infectious etiologies.

Radiological and ultrasound patterns will be classified as: pneumonia (viral or bacterial), atelectasis, or parapneumonic pleural effusion (Table 2).

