### Outcomes

The antibiotics protocol guided by LUS and PCT will be considered an improvement in the quality of care if a reduction in the prescription of antibiotics is observed, and also if there is a reduction in the number of days on antibiotics. Another primary outcome will be the increase in the sensitivity and specificity when diagnosing bacterial pneumonia using LUS. Secondary outcomes will be the reduction of the irradiation dose using the new protocol (with a reduction in economic costs as well), and a high LUS interobserver agreement.

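### The hypothesis and conclusion concern the diagnostic performance of LUS combined with PCT, but sensitivity and specificity are planned only for LUS against CXR, and under the either-positive rule these cannot stand in for the algorithm's accuracy

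*Protocol article*

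**What the plan says.** **Hypothesis and aim.** The Background gives the hypothesis: "We hypothesize that the diagnostic performance of LUS and PCT will be better than conventional CXR". The abstract's first primary aim is: "To assess whether an algorithm with LUS and procalcitonin (PCT) may be useful for diagnosing bacterial pneumonia". The Conclusion section expects the PCT and LUS algorithm to support accurate diagnosis of bacterial pneumonia.

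**Accuracy as planned.** The second main objective under Study aim is: "To analyse the sensitivity and specificity of LUS, compared to CXR, for severe community or nosocomial pneumonia". The matching primary outcome under Outcomes is the "increase in the sensitivity and specificity when diagnosing bacterial pneumonia using LUS". The main variable under Sample size is the difference between CXR and LUS. PCT appears in none of these three places.

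**The algorithm as planned.** The first main objective under Study aim is the algorithm's usefulness for indicating antibiotics and setting their duration. Outcomes matches it with prescriptions and days on antibiotics.

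**The rule (Methodology, experimental group).**
- Both negative: "If PCT is < 1 ng/mL and LUS is not suggestive of bacterial pneumonia (normal or viral), the patient will not receive an antibiotic".
- Image positive: "If LUS is suggestive of bacterial pneumonia, regardless of PCT value, an antibiotic will be recommended".
- Image negative, PCT high: "If LUS is not suggestive of bacterial pneumonia, but PCT values are > 1 ng/mL, an antibiotic will be recommended to cover other infectious etiologies".

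The control group follows the same three branches with CXR as the image, for example: "If CXR is not suggestive of bacterial pneumonia, but PCT value is > 1 ng/mL, an antibiotic will be recommended to cover other infectious etiologies".

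**The concern.** The article hypothesises about one quantity, the diagnostic performance of two tests used together, and plans to estimate another, the performance of one of them. If the plan is followed as written, its stated hypothesis is not tested. A favourable LUS result could then be reported as showing that the LUS and PCT algorithm diagnoses accurately, which is how the Conclusion section is already worded.

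This would matter less if LUS accuracy were a fair or conservative proxy for the algorithm's accuracy. For specificity it is neither, because of how the rule combines the two tests. Specificity is also the property most closely tied to the hoped-for reduction in antibiotics.

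**Working it through.** **1. Which quantity has which measure?**

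| Place in the article | Quantity | Measure |
|---|---|---|
| Abstract (first aim), Background (hypothesis), Conclusion | LUS with PCT | diagnosis of bacterial pneumonia |
| Study aim (first objective), Outcomes | LUS with PCT | antibiotic prescriptions and days |
| Study aim (second objective), Outcomes | LUS against CXR | sensitivity and specificity |
| Sample size | LUS against CXR | difference in proportions |

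No row pairs LUS with PCT and sensitivity or specificity. The hypothesis also names conventional CXR as comparator, whereas the control group is managed by CXR with the same PCT rule.

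The article gives no accuracy figure for the combined rule, so there is none to reproduce. Its 63 per group cannot be re-derived either, because no proportions are stated. Nothing below depends on it.

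**2. The rule written out.** A PCT of exactly 1 ng/mL is not assigned by the text and is left aside.

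| Image | PCT > 1 ng/mL | Image alone | Rule | Change |
|---|---|---|---|---|
| – | – | no | no | 0 |
| – | + | no | antibiotic | +1 |
| + | – | antibiotic | antibiotic | 0 |
| + | + | antibiotic | antibiotic | 0 |

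PCT changes one cell of four, and only towards an antibiotic.

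**3. Consequence for accuracy.** Every image-positive child is rule-positive. With D the reference diagnosis:

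- Se(rule) = Se(image) + P(image –, PCT + | D present) ≥ Se(image)
- Sp(rule) = Sp(image) − P(image –, PCT + | D absent) ≤ Sp(image)

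This is set inclusion. It holds for any values and needs no independence assumption.

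**4. Illustration of size.** All accuracy inputs are assumed, the tests are taken as conditionally independent, and the image-negative, PCT-high branch is scored as positive for bacterial pneumonia. Then Se = 1 − (1 − Se_LUS)(1 − Se_PCT) and Sp = Sp_LUS × Sp_PCT.

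- LUS 90%/90% and PCT 70%/80% (sensitivity/specificity): Se = 1 − 0.10 × 0.30 = 0.97; Sp = 0.90 × 0.80 = 0.72.
- Other specificities: 0.90 × 0.70 = 0.63; 0.80 × 0.80 = 0.64; 0.80 × 0.70 = 0.56.

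The combined specificity is therefore 56–72% where LUS alone has 80–90%. These figures show only that the gap could be large. They are not a result for this trial.

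**The case against.** The strongest case against has four parts.

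**The algorithm does have outcomes.** This stands. The body of the article frames the algorithm's objective as guiding antibiotic treatment, and prescriptions and days match that objective. A reader might infer that the algorithm is not evaluated at all, or that PCT's contribution cannot be recovered. The documents do not support either reading: the algorithm is evaluated on antibiotic use, and image and PCT are both needed to classify each child. What is missing is an accuracy measure for the combination, which is what the hypothesis and the abstract's first aim call for.

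**LUS alone is not a comparator in this trial.** This also stands, and it limits the claim. A reader might infer that PCT can only increase prescribing. That is true only relative to the image alone, and only for starting treatment. Against unguided practice, a low PCT with a negative image may mean fewer antibiotics, and the truth table does not address duration. The article nowhere claims that PCT lowers prescribing relative to LUS alone.

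**The image-negative, PCT-high branch is not a pneumonia diagnosis.** The rule treats those children for other infections, so scoring them as false positives for pneumonia is open to dispute. This stands against quoting 97% and 72% as findings. It does not rescue the hypothesis. If that branch is not a pneumonia diagnosis, the algorithm's diagnostic classification equals the LUS result, and PCT contributes nothing to the diagnostic performance claimed for the combination.

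**The extra tables belong in an analysis plan.** True of the tabulation. The mismatch, however, is between statements the article makes explicitly about its hypothesis, objectives, outcomes and conclusion. A further table elsewhere would not remove it.

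**Conclusion.** The point holds in this form: the article hypothesises and concludes on the diagnostic performance of LUS with PCT, while its accuracy objective, accuracy outcome and sample-size variable concern LUS against CXR. The planned accuracy result cannot be transferred to the algorithm, because relative to the image alone the rule's sensitivity can be no lower and its specificity no higher. This direction follows from the three branches alone.

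The size of the difference cannot be determined from the article. The 56–72% range rests on assumed test characteristics, on conditional independence, and on scoring the image-negative, PCT-high branch as pneumonia. A reader might take from it that the algorithm's specificity is known to be lower than that of LUS; the documents support only that it is no higher.

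The antibiotic outcomes and the LUS against CXR comparison are untouched by this point. What changes is the claim of diagnostic accuracy for the combined algorithm, which the plan as written would not support.

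**What to change.** Leave the treatment rule as it is and do one of the following.

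**(a) Estimate what is claimed.** In each arm, report the sensitivity and specificity of the combined rule (LUS or PCT; CXR or PCT) beside those of the image alone, with the image-by-PCT table. The reference diagnosis must not contain the PCT criterion. The community pneumonia definition under Definitions lists PCT above 1 ng/mL among its laboratory criteria, so using it as the reference would build in incorporation bias. That definition also includes the image, so the same caution applies to the image results. Report separately the image-negative children with PCT above 1 ng/mL who are treated for other infections, so that readers can see the effect of counting them either way.

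**(b) Claim only what is estimated.** Restate the hypothesis, the abstract's first aim and the Conclusion section as LUS against CXR within a common PCT rule, and make no claim about the diagnostic accuracy of LUS with PCT.

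The cost is small. Option (a) is a modest extra analysis of image and PCT results already needed to classify patients, plus a PCT-free reference diagnosis. Its drawback is that the algorithm's specificity may look less favourable than that of LUS alone. Option (b) is rewording only, and gives up the claim about the combination.

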## Methods and design

The study is designed as a randomized, blinded clinical trial of children with severe community or nosocomial pneumonia. It will be conducted at a single PICU at Sant Joan de Déu Hospital, a tertiary children’s hospital in Barcelona. Period of recruitment and follow-up was from September 2017 to December 2019.

### Study aim

Our primary goal is to improve the quality of care in children with suspected community or nosocomial pneumonia in a PICU.

The main objectives are:
To assess whether a diagnostic algorithm for pneumonia that combines LUS and PCT may be useful in indicating and determining the duration of antibiotic treatment.To analyse the sensitivity and specificity of LUS, compared to CXR, for severe community or nosocomial pneumonia.

The secondary aims are:
To quantify the irradiation dose avoided using LUS to replace CXR, and to determine if there is an associated decrease in costs.To analyse interobserver agreement in LUS

### Inclusion and exclusion criteria

Inclusion: Children under 18 years old with suspected community pneumonia who require admission to the PICU or patients with suspected nosocomial pneumonia during their PICU stay.

Exclusion: Patients with underlying pathologies such as cystic fibrosis or who are immunocompromised. Patients who develop nosocomial pneumonia after being included in the study due to community pneumonia. Patients who have a CXR taken before being admitted to the PICU.

Withdrawal and abandonment criteria: Violation of study protocol, withdrawal of parental consent, death.

Patients withdrawing or with loss of protocol adherence will be excluded from the study.

### Definitions

Community pneumonia: Patients with compatible clinical suspicion (fever, cough, tachypnoea, shortness of breath, abnormal respiratory auscultation sounds, hypoventilation, tubular breath sounds, thoracic or abdominal pain), compatible CXR (lobar consolidation, airspace opacity, pleural effusion, bullae, etc.) or LUS, changes in blood with a C-reactive protein higher than 50 mg/L and/or PCT higher than 1 ng/mL.Nosocomial pneumonia: Based on the Clinical Pulmonary Infection Score (CPIS) (Table 1).Ventilator-associated pneumonia: defined according to the Center for Disease Control criteria (CDC).

### LUS procedure

LUS will be performed by any of the 8 intensive care physicians who have received standard training in LUS (Winfocus PNCUS BL1P) and who have at least 3 years of experience using it. Team sessions focusing on the diagnosis of pneumonia with LUS will be repeated every 3 months to ensure quality and consistency in the LUS exam. The supplemental data included in the Shah et al. article will be used [26].

Subjects will be examined while they are in supine position. Imaging will be performed using a portable ultrasound device (Toshiba® Xario 200). A 12-MHz linear or a 5-MHz convex probe will be used, depending on the weight or size of the patient. A scan will be taken systematically in 3 areas for each hemithorax (anterior, lateral, and posterior), according to international recommendations [27]. Each area will be examined longitudinally and transversally.

In each area the following will be evaluated [27]: A-lines, B-lines (number and distance between them), lung sliding (M-mode), pleural space, lung consolidations, small subpleural consolidations, dynamic air bronchogram, vascular pattern, presence of lung point, and lung pulse.

The determination of a bacterial pneumonia ultrasound pattern will be based on the presence of lung consolidation with air bronchograms, which in initial stages are detected as small subpleural hypoechoic zones of less than 1 cm with bronchogram (not seen using conventional CXR) [28–31]. The determination of a viral pneumonia ultrasound pattern will be based on the presence of B-lines or coalescent B-lines with small subpleural consolidations of less than 1 cm, without bronchogram [32, 33].

### Methodology

The first thing to do will be to obtain consent from the parent(s) or legal guardian(s).

Patients who meet the inclusion criteria and sign the inform consent were randomly assigned to two groups using the “random” function in MS-Excel XP® program. A binary series of random numbers were generated according to the procedure described by Friedman. To procure a similar number of patients in both groups, the procedure created the sequence through a balanced block sampling. The series of numbers were held by the principal investigator and depending on the number of the patient tit was be assigned to on or another group. A total of 8 physicians enrolled participants, and the principal investigator assigned participants to interventions, depending on the randomized list. (Fig. 1)
Experimental Group 1: The paediatrician-researcher (PR) performs the LUS at admission/suspicion as the first lung image test. If the paediatrician assistant (PA) requires a CXR, it can be performed, but the PR will not see the CXR. Patients will be subdivided into 3 groups:
If PCT is < 1 ng/mL and LUS is not suggestive of bacterial pneumonia (normal or viral), the patient will not receive an antibiotic.If LUS is suggestive of bacterial pneumonia, regardless of PCT value, an antibiotic will be recommended.If LUS is not suggestive of bacterial pneumonia, but PCT values are > 1 ng/mL, an antibiotic will be recommended to cover other infectious etiologies.Control Group 2: CXR will be performed as a first lung image test. Criteria to start an antibiotic will depend on the current unit protocol.
If PCT is < 1 ng/mL and CXR is not suggestive of bacterial pneumonia (normal or viral), the patient will not receive an antibiotic.If CXR is suggestive of bacterial pneumonia, regardless of PCT value, an antibiotic will be recommended.If CXR is not suggestive of bacterial pneumonia, but PCT value is > 1 ng/mL, an antibiotic will be recommended to cover other infectious etiologies.

Radiological and ultrasound patterns will be classified as: pneumonia (viral or bacterial), atelectasis, or parapneumonic pleural effusion (Table 2).

LUS will be performed every day following admission and recorded and stored. LUS images will be later analysed by a paediatric radiologist who is an expert in LUS and who has not seen the initial assessment and CXR, in order to evaluate interobserver agreement. CXR will be also be reported on by a paediatric radiologist consultant who has not seen the other results.

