### Data collection

The study coordinator will register patients, verifying compliance with all the inclusion criteria. An external company will be appointed to monitor the study and ensure compliance with correct clinical practice principles (ICHE6). Once the notebooks are audited, they will be entered into a validated database, one with restricted access by user level, which is equipped with inconsistency detection filters, and which affords data traceability until the database is no longer needed.

Data access: All the physicians and clinical researchers involved in the study, the Ethics Committee, and the relevant health authorities will have access to the data.

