### Sample size

Sample size calculations will be performed using the statistical program Ene 2.0®. The main variable will be the existence of differences between CXR and LUS in patients with community pneumonia and nosocomial pneumonia. H1 will be considered as the existence of differences between LUS and CXR. An 80% power will be required to detect differences in the contrast of the null hypothesis H0: p1 = p2, using a bilateral X^2^ test for two independent samples. If we consider a significance level of 5%, it will be necessary to include 63 units in the control group and 63 units in the experimental group. A total of 126 patients will be included for community pneumonia. Twenty-eight patients per group will be included for nosocomial pneumonia; therefore, there will be 56 patients in total for this kind of pneumonia. After 12 months of recruitment, a preliminary analysis will be carried out to guarantee the safety of the patients. Respiratory infection represents around 30–70% of the PICU admissions, depending on the season. There will be an estimated 200–300 recruitable patients per year, so it is expected that the calculated sample size will be attainable.

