### Statistical analysis

Using the “Random” function of the MS-Excel XP® program, a binary series of random numbers will be generated, according to the procedure described by Friedman [34]. This procedure creates the sequence by means of balanced block sampling to ensure a similar number of patients in each group. The series of numbers will be in the possession of the PICU’s head researcher. Depending on that number, each patient will be assigned to one group or the other. If a patient is randomized but does not complete the treatment, their data will not be analysed, and their random number will not be reused.

The categorical variables will be compared using the Chi-square test. The quantitative analysis will be compared using Student’s t-test or the Mann-Whitney U test, depending on whether the sample follows a normal distribution or not. A multivariate logistic regression analysis will be performed on those variables with statistical significance or a clear tendency in the univariate analysis to detect which factors represent a protective factor or not, in terms of quality. The analysis of the interobserver agreement will be performed using Cronbach’s alpha. A *p* < 0.05 will be considered significant. The statistical program SPPS® 20.0 will be used.

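### An investigator in the recruiting unit holds the whole blocked allocation series and assigns from it, and one series balanced only overall does not guarantee the 63/63 and 28/28 splits

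*Protocol article*

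**What the plan says.** On custody, the Methodology section states "The series of numbers were held by the principal investigator" and adds that "the principal investigator assigned participants to interventions, depending on the randomized list", while 8 physicians enrol. The Statistical analysis section repeats the arrangement: "The series of numbers will be in the possession of the PICU’s head researcher". The two role titles differ and may or may not mean one person; either way the holder is an investigator of the unit where patients are recruited.

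On the sequence, Methodology describes a single series: "A binary series of random numbers were generated according to the procedure described by Friedman". Its aim is "To procure a similar number of patients in both groups", and "the procedure created the sequence through a balanced block sampling". Neither block size nor strata are mentioned.

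On size, the Sample size section treats the two pneumonia types separately. For community pneumonia "it will be necessary to include 63 units in the control group and 63 units in the experimental group"; for nosocomial pneumonia it gives 28 per group.

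On masking, the opening of Methods and design calls the trial blinded. Methodology then keeps the researcher in the ultrasound arm from seeing the chest X-ray, and has radiologists read images without the other results.

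**The concern.** Concealment requires that whoever influences entry to the trial cannot know the next allocation. Here the full list sits with an investigator in the unit who also applies it, and no step is described that hides the next number from that person. Eligibility rests on clinical suspicion, so there is discretion over whom to enrol and when. Two of the primary outcomes, antibiotic prescription and days on antibiotics, are decided by clinicians in the same unit. If foreknowledge influenced enrolment, the arms would differ at baseline in ways that analysis cannot reliably repair.

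The second part is a mismatch between the size calculation and the sequence. Per-group numbers are fixed within each pneumonia type, but the balance aimed for is overall. The comparisons named in the Statistical analysis section are not stratified by type. The logistic regression admits variables only if the univariate result is significant or shows a clear tendency, so type is not assured a place in it.

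**Working it through.** **Custody.** No arithmetic applies. Set side by side, Methodology gives possession of the series and the act of assignment to one role, and Statistical analysis confirms that the series stays within the unit. Foreknowledge by the list holder follows directly. Foreknowledge by the 8 enrolling physicians does not: it needs the holder to be one of them, or to disclose, or the block size to be known or guessable from past allocations.

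**The plan's own figures.** The usual pooled-variance formula for a two-sided chi-square test at 5% with 80% power is n per group = [1.96·√(2p̄(1−p̄)) + 0.84·√(p1(1−p1) + p2(1−p2))]² / (p1 − p2)². The article gives neither p1 nor p2, so 63 and 28 can be neither confirmed nor refuted. Many pairs fit: 0.30 against about 0.545 gives 63, and 0.30 against about 0.67 gives 28.

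**Split within type under one list.** Inputs: total 126 + 56 = 182, hence 91 per arm on a balanced list; 56 nosocomial patients. Assumption: the two types arrive in random order. The number X of nosocomial patients in one arm is then hypergeometric (182, 91, 56).

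1. Mean = 56 × 91/182 = 28.
2. Variance = 56 × ½ × ½ × (182 − 56)/(182 − 1) = 14 × 126/181 = 9.75, so SD = 3.12.
3. P(X = 28) = C(91,28)²/C(182,56) = 0.127.
4. P(3 or more away from 28) = 0.42; P(24/32 or worse) = 0.26.
5. The 95% range is 22/34 to 34/22. Subtracting from 91, the community range is 57/69 to 69/57.

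Simulated permuted blocks of 2, 4, 6, 8, 10 and 14 (4000 runs each) gave SDs of 3.11 to 3.18 and P(28/28) of 0.118 to 0.134, so block size hardly matters.

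**Power at the ends of the range.** The rates are assumed, chosen so that 28 or 63 per group is the required size.

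| Type | Assumed rates | Equal split | Less favourable end of the range |
|---|---|---|---|
| Nosocomial | 0.10 vs 0.429 | 0.815 | 0.783 (22/34) |
| Nosocomial | 0.30 vs 0.672 | 0.813 | 0.795 (22/34) |
| Nosocomial | 0.50 vs 0.849 | 0.814 | 0.786 (34/22) |
| Community | 0.10 vs 0.299 | 0.806 | 0.797 (57/69) |

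The largest loss is 0.815 − 0.783 = 0.032 for nosocomial and 0.806 − 0.797 = 0.009 for community pneumonia.

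**Effect on a pooled comparison.** With a 24/32 split in arms of 91, nosocomial patients make up 24/91 = 26.4% and 32/91 = 35.2%, a gap of 8.8 percentage points. The article gives no antibiotic rates by type. If they differed by an assumed 20 to 40 points, the pooled arm difference would shift by 0.088 × 20 = 1.8 to 0.088 × 40 = 3.5 points.

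**The case against.** The stratification part rests on inference. The article describes one series and is silent on strata; it condenses a fuller protocol, and separate lists may exist. That stands, and it is why stating that they exist would settle this part.

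A reader might infer that the 63/63 and 28/28 splits will not be delivered. The documents do not support that: both are the expected splits under one balanced list, and the accurate word is not guaranteed. Nor would two lists secure the analysed numbers, since withdrawals and non-completers are dropped and their random numbers are not reused.

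A reader might also infer that the pooled result is confounded. No section commits to a pooled analysis. Within each type the randomised comparison is unaffected by imbalance between types, and chance imbalance is not systematic bias. The point applies only if the types are pooled.

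On concealment, a reader might call this an open trial whose allocations the recruiting doctors could foresee. The article labels the trial blinded and does mask image reading; what can be said is that the bedside team cannot be blind to the arm. Methodology also separates enrolment by 8 physicians from assignment by the principal investigator and puts consent first, and Data collection has a coordinator check eligibility. These safeguards help, but none hides the sequence from the person who assigns.

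**Conclusion.** The concern holds in limited form. The custody part is stated outright, twice, and is the stronger: an investigator in the recruiting unit both knows and applies the sequence. The size of any resulting selection bias cannot be derived from the article, and foreknowledge is established for the list holder only.

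The balance part is modest. If there is one unstratified list, 28/28 is not guaranteed (SD about 3 per arm, about a 13% chance of an exact split). The power cost is about 3 percentage points at most in nosocomial and about 1 point in community pneumonia. A pooled antibiotic comparison could move by about 2 to 4 points at a 24/32 split under the assumed rate differences. These figures assume 91 per arm before exclusions and types arriving in random order; where runs of one type fill whole blocks, the imbalance would be smaller.

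**What to change.** - Use one blocked list for community and one for nosocomial pneumonia, or state that these exist, with varied and undisclosed block sizes. Type is known at enrolment, because the inclusion criteria separate the two.
- Give custody to a party with no enrolment or care role. One is already foreseen: "An external company will be appointed to monitor the study". Release each allocation singly, after consent and registration; numbered opaque envelopes would do.
- Analyse any pooled antibiotic outcome stratified by pneumonia type (Mantel-Haenszel) or adjusted for it by prior specification, rather than leaving type to univariate selection.
- In Methods and design, say who is blinded and to what.

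The cost is a second list, a handover of custody and a small logistics effort at enrolment. Methods and design reports recruitment in the past tense, from September 2017 to December 2019. If it is complete, the first two changes are no longer possible; the type-stratified analysis, the clarification of blinding and a stated limitation on list custody still are, at almost no cost.
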